### Phase II: expert review

The 180 videos are reviewed with a different focus by an expert panel consisting of clinicians and academics in the field of cardiology, endocrinology, epidemiology, psychology and linguistics. First, the clarity, accuracy and feasibility of each video is checked and verified. Second, linguists review all videos and focus on the acceptability and readability of the video education material. Issues regarding videos are addressed, and the corresponding education videos are shot again in order to achieve the desired target which the expert panel had proposed.

### Frequency and timing of education video delivery

One hundred eighty coaching videos in total are pushed forward to the participants in the intervention group across a 6-month timeframe. The videos are sent to the participant portal every 2 days in the morning. The theme of the coaching video covers a range of recommendations from the recent guidelines. Participants in the intervention group will receive the updated text message and log into the WeChat-based miniprogram to read the updated educational video material. Initially, only one education video is available. To evaluate the engagement in the miniprogram system, participants are required to finish the question at the end of every video, “Do you think that the information is easy to understand? Do you think that information is useful?”. The logbook data are analyzed at the completion of the study intervention. Through the 6-month follow-up, research staff call participants if they do not finish the questions for two consecutive weeks and only one call is made per patient during the intervention period, so as not to confound the intervention. Patient communication is delivered by automated feedback on the mobile phone WeChat-affiliated miniprogram and messaging through the message centre in the patient web portal.

### Data collection and management

Patient characteristics are collected from self-reported interviews with trained research staff and medical chart reviews including basic information, baseline clinical variables, biochemistry information, coronary angiography, echocardiographic outcomes, diabetes-related variables, surgical details, postoperative complication and socioeconomic status (Supplementary materials).

Additional assessments of baseline medication adherence, health status (EuroQol five-dimensional questionnaire: EQ-5D), are also conducted in person [20]. Biochemistry tests will be analysed at the central laboratory. The process of recruitment is monitored and data collection is checked by trained staff from China National for Cardiovascular Disease to improve the quality control.

A specialized software platform is established by the Information Technology team for use in sending coaching video materials to participants and also recording responses. In addition, project progress can be supervised and 24-h management support is provided through this web-based platform. Predesigned onscreen case report form is entered by two staff members independently, and data are then securely transmitted to the central server through automatic electronic transfer. Continuous checks are run to ensure that data being entered are complete and meet predefined data formats and ranges to ensure the reliability and validity of the data.

The database is regularly backed up and password protected so that only a limited number of approved staff members can have access to the data. Data confidentiality policies of NCCD on data collection, storage and analysis have been strictly imposed to ensure the confidentiality.

### Outcomes

The primary outcome is the change in glycaemic HbA_1c_ by the central blood sample. Secondary outcomes include blood pressure, blood glucose, low-density lipoprotein, a change in the proportion of patients achieving HbA_1c_ < 7% of patients, graft patency, major adverse cerebrovascular and cardiovascular events (MACCEs), change in medication adherence, mini-program behaviour adherence, changes in antihyperglycaemic medications during the intervention and health status (EQ-5D). MACCEs include death, non-fatal myocardial infarction, stroke and any repeated revascularization and cardiac rehospitalizations. HbA_1c_ is determined using a high-performance liquid chromatography technique with ADAMS A_1c_HA-8180 (ARKRAY, Japan). Graft outcomes are assessed by multislice computed tomographic angiography (MSCTA) or catheter coronary angiogram (CAB) at 6 months after coronary artery bypass grafting. The examinations are conducted according to standardized radiology and cardiology procedures. Digital images from a ≥ 64-slice CT scanner are analyzed with software (Intellispace portal Version 6.0, Phillips Healthcare). Members of the independent Image Data Review Centre reviewed the images and adjudicated the patency of the grafts blinded to treatment assignments.

Graft patency is defined according to FitzGibbon criteria [21]. In our trial, graft patency is defined as FitzGibbon grade A [22, 23]. Quality of life is measured using the short version of EQ-5D.

The institutional follow-up protocol requires that patients who are discharged alive visit our outpatient clinic 3 and 6 months after coronary artery bypass graft. If adverse events are reported, the patient medical records in the outpatient clinic were checked cautiously. When the patients visited another hospital, they are asked to send copies of their medical records by mail. If the patient dies at home without any evidentiary material, a structured summary of death conversation with family members would be reported. All information is sent to NCCD for central adjudication according to prespecified criteria by trained clinicians.

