**Methods:**

The glycaemic control using miniprogram-based intervention in patients with diabetes undergoing coronary artery bypass to promote self-management (GUIDE ME) study is a multi-centre, randomized controlled trial of mobile intervention versus standard treatment with 6 months follow-up conducted in 2 hospitals in China. The interventions are education and a reminder system based on the WeChat mini-program. Participants in the intervention groups receive 180 videos (including lines) about secondary prevention education for 6 months as well as the standard treatment. Behavioural change techniques, such as prompting barrier identification, motivational skills, and goal setting, are employed. A total sample size of 820 patients would be adequate for the GUIDE ME study. The primary outcome is the change of glycaemic haemoglobin (HbA_1c_) at 6 months. Secondary outcomes include a change in the proportions of patients achieving HbA_1c_, fasting blood glucose, systolic blood pressure, low-density lipoprotein cholesterol (LDL-C) and medication adherence.

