### Statistical analysis

All analyses will be conducted according to the intention-to-treat principle. Baseline patient characteristics are represented as the means with standard deviations (SDs) for continuous variables and proportions for categorical variables. The primary analysis will use an analysis of covariance. For categorical secondary outcomes, log-binomial regression is used to compare groups and calculate the relative risk of outcomes at 6 months (ie, proportions of patients achieving HbA_1c_ < 7.0%). A generalized estimating equation model including terms for treatment is used to estimate between-group differences in graft patency and 95% confidence intervals (CIs). For the (time-to-event) secondary outcomes, hazard ratios (HRs) and corresponding 95% CIs are determined with Cox proportional hazards regression analysis. Kaplan–Meier curves are used to depict the occurrence of secondary outcomes over time. Follow-up of event-free patients with incomplete follow-up will be censored at the last clinical contact. Additionally, we performed prespecified subgroup analyses of outcomes by age (< 60 and ≥ 60 years), sex (male and female), area (urban and rural), education (≤ 12 and > 12 years) and tertile of baseline HbA_1c_. Subgroup results are presented as mean differences with 95% CIs. All tests of significance are 2-tailed, with an a of 0.05.

We estimate that a sample size of 820 would provide 80% power at the 5% significance level to detect a 0.3% absolute difference in HbA_1c_ change in the intervention group at 6 months, compared with the control group, assuming a mean HbA_1c_ level of 7.0% at baseline (SD 1.4%) based on data from studies involving similar populations [24], using PASS, version 11.0 (NCSS, Kaysville, UT), for sample size calculation. This sample size allows for a 20% loss to follow-up during the study period. We used the SPIRIT checklist when writing our report [25].

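### The HbA1c <7% secondary outcome is worded as a change in a proportion but analysed as a 6-month relative risk; separately, that model states no baseline HbA1c term, which, if run as written, costs precision but not validity

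*Protocol article*

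**What the plan says.** Three places in the protocol article bear on this outcome.

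- **Outcomes:** the secondary outcomes include "a change in the proportion of patients achieving" HbA1c <7%.
- **Abstract, Methods:** "Secondary outcomes include a change in the proportions of patients achieving HbA_1c", followed by a list of other risk factors that ends with medication adherence.
- **Statistical analysis:** for categorical secondary outcomes, "log-binomial regression is used to compare groups and calculate the relative risk of outcomes at 6 months". The example given is "proportions of patients achieving HbA_1c_ < 7.0"%, so the model is meant for this endpoint.

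No covariate is named for the log-binomial model. None is named for the primary model either: "The primary analysis will use an analysis of covariance".

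Baseline HbA1c is available, because the Statistical analysis section plans subgroups by its tertiles. It is not among the minimisation factors under Allocation sequence generation (age, gender, education, history of acute myocardial infarction, insurance type).

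**The concern.** There are two separate issues.

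**Definition.** A change in a proportion uses attainment at baseline as well as at 6 months. A relative risk of 6-month proportions uses 6 months only. The two would nearly coincide if almost nobody were below 7% at entry, but the Inclusion and exclusion criteria set no HbA1c threshold and the planning assumption is a mean "level of 7.0% at baseline (SD 1.4"%). If HbA1c is roughly symmetric, about half the patients start below 7%, so the two readings can give different estimates and different power. With both on the page, the choice could be made after the results are known.

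**Baseline adjustment.** Baseline HbA1c can be expected to predict 6-month HbA1c, and the allocation scheme does not balance it. A model without it leaves usable information aside. What is at stake is the precision of one secondary outcome; the primary analysis is not affected.

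**Working it through.** **1. The plan's own figure.** With difference 0.3, SD 1.4, two-sided 5% and 80% power, n per arm = 2 × (1.960 + 0.842)² × 1.4² / 0.3² ≈ 342, or 684 in total. 684 × 1.2 = 821, which matches the stated 820. (684 / 0.8 would be 855; nothing below depends on this.) The document states no power for the HbA1c <7% outcome. After the planned 20% loss, 410 × 0.8 = 328 completers per arm.

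**2. Assumptions not in the document.** 6-month HbA1c is normal with SD 1.4; the control mean is 7.0 and the intervention mean 6.7; the correlation r between baseline and 6 months is 0.3, 0.5 or 0.7.

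**3. Expected proportions below 7%.** Control: Φ(0) = 50.0%. Intervention: Φ(0.3/1.4) = 58.5%. The relative risk is 1.17 (log 0.157) and the difference 8.5 points.

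**4. Unadjusted 6-month comparison.**
- Difference scale: SE = √[(0.25 + 0.585 × 0.415)/328] = 0.0388; power ≈ Φ(0.0848/0.0388 − 1.96) = 59%.
- Log relative risk scale: SE = √[(0.5/0.5 + 0.415/0.585)/328] = 0.0722; power ≈ Φ(0.157/0.0722 − 1.96) = 58%.

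**5. Variance relative to the unadjusted comparison.** For a split at the median, the correlation between baseline and 6-month attainment is φ = (2/π) arcsin r.
- Literal difference in change of proportion: 2(1 − φ).
- Adjusted for baseline status below 7%: 1 − φ².
- Adjusted for continuous baseline HbA1c: 1 − (2/π) arcsin(r²).

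Each cell gives the variance ratio, then power on the difference scale.

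| Analysis | r = 0.3 | r = 0.5 | r = 0.7 |
|---|---|---|---|
| Unadjusted, 6 months | 1.00; 59% | 1.00; 59% | 1.00; 59% |
| Literal change in proportion | 1.61; 41% | 1.33; 47% | 1.01; 59% |
| Adjusted, baseline <7% status | 0.96; 61% | 0.89; 64% | 0.76; 71% |
| Adjusted, continuous baseline | 0.94; 62% | 0.84; 67% | 0.67; 76% |

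**6. Simulation check** (1,500 trials per correlation; adjusted estimate standardised from a logistic model). The SD of the log relative risk was 0.0727 / 0.0735 / 0.0744 unadjusted and 0.0707 / 0.0674 / 0.0605 adjusted. Squared ratios are 0.95 / 0.84 / 0.66, a reduction of 5% / 16% / 34%. The mean log relative risk was about 0.155 both ways, so adjustment changes precision and not the target. At r = 0.3 the adjusted mean and SD give Φ(0.1565/0.0707 − 1.96) = 60%. A further simulation of 4,000 trials gave power of 57% unadjusted and 66% adjusted at r = 0.5, and 58% and 75% at r = 0.7. The unadjusted power does not depend on r; the 57% against 58% is simulation noise.

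**7. Chance imbalance.** The SE of the baseline difference in the proportion below 7% is √(0.25 × 2/328) = 3.9 points. Only a fraction φ carries over to 6 months: 3.9 × 0.194 = 0.8 points at r = 0.3 and 3.9 × 0.494 = 1.9 points at r = 0.7. This is already inside the unadjusted standard error and is not an additional bias.

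**8. Model choice.** With treatment alone, a log-binomial model reproduces the two arm proportions and fits without trouble. With continuous baseline HbA1c at 50-58% prevalence, the log link pushes fitted probabilities above 1, and in simulation most such fits failed.

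**The case against.** The strongest reply is that the document never says the log-binomial model is unadjusted. It lists no covariates for any model, including the analysis of covariance, and a covariate list is commonly left to the full protocol or SAP, neither of which is shown. This stands. A reader might infer that the plan has chosen to ignore baseline, but that would be reading a decision into silence, so the precision loss is stated here only as what follows if the model is run as written.

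A second tempting inference is that the mismatch between outcome and analysis loses precision. It does not: the literal change in proportion would be less precise than the stated 6-month comparison at r = 0.3 and 0.5, and about equal at 0.7. The Statistical analysis section already names the equal or better contrast.

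A third is bias. Under randomisation the expected baseline proportions are equal, so on the difference scale both contrasts target the same effect.

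It is also fair that the size rests on a correlation the document does not give, that at r = 0.3 the gain is small, and that the share below 7% at baseline depends on an assumed symmetric distribution. The convergence problem arises only once a continuous covariate is added, so it is a reason for the choice of adjusted estimator and not an error in an unadjusted log-binomial model.

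What remains is that the two sections describe different quantities, and that a more precise analysis is available from data already collected.

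**Conclusion.** The wording inconsistency is established from the document itself. It is minor, concerns one secondary outcome, and affects neither the validity nor the precision of the planned comparison.

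The baseline point is conditional. If the model is run with no baseline term, the estimate is unbiased but less precise than it could be. Under normal HbA1c, SD 1.4, effect -0.3, 328 completers per arm and correlation 0.3 to 0.7, adjustment for continuous baseline HbA1c reduces the log relative risk variance by about 5% to 34%. Power rises from about 57-59% to about 60-76%; the ranges cover the two scales, the simulations and the assumed correlations. At the low end this is a small gain and at the high end a worthwhile one. No stated figure in the protocol is contradicted, because the 820 was sized on mean HbA1c change.

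**What to change.** 1. In Outcomes, define this secondary outcome as the proportion of patients with HbA1c <7.0% at 6 months.
2. In the Abstract, reword only the HbA1c item to match. Do not simply delete the word change there: it also governs medication adherence, which Outcomes does define as a change.
3. In Statistical analysis, state that the 6-month relative risk is adjusted for baseline HbA1c as a continuous covariate, estimated by logistic regression with standardisation over the trial population, or by modified Poisson regression with robust standard errors, in place of log-binomial regression. The gains given above were calculated for the standardised logistic estimate. If the full protocol or SAP already names baseline HbA1c for this model, only the choice of estimator needs checking.

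The cost is two wording edits, one revised model sentence and a little analysis code. No new data are needed, since the planned tertile subgroups already require baseline HbA1c.

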#### Access to data

The data and statistical code are not available to be shared at this time as no datasets are analysed during the current study. The final dataset can be available at the end of this study after contact with the corresponding author.

#### Ancillary and post-trial care

In our study, there is no provision for ancillary and post-trial care. The intervention group participants will not receive any reminder nor coaching video after the study.

### Statistical analysis

All analyses will be conducted according to the intention-to-treat principle. Baseline patient characteristics are represented as the means with standard deviations (SDs) for continuous variables and proportions for categorical variables. The primary analysis will use an analysis of covariance. For categorical secondary outcomes, log-binomial regression is used to compare groups and calculate the relative risk of outcomes at 6 months (ie, proportions of patients achieving HbA_1c_ < 7.0%). A generalized estimating equation model including terms for treatment is used to estimate between-group differences in graft patency and 95% confidence intervals (CIs). For the (time-to-event) secondary outcomes, hazard ratios (HRs) and corresponding 95% CIs are determined with Cox proportional hazards regression analysis. Kaplan–Meier curves are used to depict the occurrence of secondary outcomes over time. Follow-up of event-free patients with incomplete follow-up will be censored at the last clinical contact. Additionally, we performed prespecified subgroup analyses of outcomes by age (< 60 and ≥ 60 years), sex (male and female), area (urban and rural), education (≤ 12 and > 12 years) and tertile of baseline HbA_1c_. Subgroup results are presented as mean differences with 95% CIs. All tests of significance are 2-tailed, with an a of 0.05.

We estimate that a sample size of 820 would provide 80% power at the 5% significance level to detect a 0.3% absolute difference in HbA_1c_ change in the intervention group at 6 months, compared with the control group, assuming a mean HbA_1c_ level of 7.0% at baseline (SD 1.4%) based on data from studies involving similar populations [24], using PASS, version 11.0 (NCSS, Kaysville, UT), for sample size calculation. This sample size allows for a 20% loss to follow-up during the study period. We used the SPIRIT checklist when writing our report [25].

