### Allocation sequence generation

Participants are randomly allocated to enter the intervention or the control arm in a 1:1 ratio using a computerized randomization system using minimization. In order to achieve a balance of participants’ characteristics in both arms, a stratified randomization approach is employed, based on age, gender, education degree, acute myocardial infarction history and medical insurance type.

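### On the printed inputs, 820 patients with 20% loss give about 78% power rather than 80%; the figures need a small restatement, not more patients

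*Protocol article*

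**What the plan says.** The sample size paragraph at the end of the Statistical analysis section gives every input that a two-group comparison of means needs.

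- Size, power and level: "We estimate that a sample size of 820 would provide 80% power at the 5% significance level".
- Effect: "to detect a 0.3% absolute difference in HbA_1c_ change in the intervention group at 6 months", compared with control.
- Spread: "assuming a mean HbA_1c_ level of 7.0% at baseline (SD 1.4"%), taken from earlier studies in similar populations.
- Loss: "This sample size allows for a 20% loss to follow-up during the study period".

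The same section fixes the sidedness: "All tests of significance are 2-tailed, with an a of 0.05". It names analysis of covariance as the primary analysis. Allocation is given under Allocation sequence generation: "Participants are randomly allocated to enter the intervention or the control arm in a 1:1 ratio". The Methods part of the abstract repeats the total: "A total sample size of 820 patients would be adequate for the GUIDE ME study".

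The article prints neither the number of evaluable patients nor the formula used to allow for loss.

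**The concern.** The paragraph makes two claims about the same 820 patients: that they give 80% power, and that this already covers a 20% loss. On the printed inputs both cannot be true. Read as written, a team that loses a full 20% would believe it still has 80% power on the primary outcome, when the unadjusted calculation gives slightly less. The loss that 820 can absorb is overstated, at 20% against about 16%. The figure supports the power claim for the primary endpoint and is repeated in the abstract, so it should be one that a reader can reproduce.

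**Working it through.** **Inputs.** Difference 0.3, SD 1.4, two-sided alpha 0.05, power 80% and loss 20% (all from Statistical analysis); 1:1 allocation (Allocation sequence generation). The SD is given for HbA1c at baseline. I use it as the outcome SD because it is the only one printed.

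**1. Evaluable patients needed.**

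n per arm = 2 × (1.96 + 0.8416)² × 1.4² / 0.3² = 341.9, so 342 per arm and 684 in total.

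With the t distribution it is 342.8, so 343 per arm and 686 in total.

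**2. Allowance for 20% loss.** The number randomised must leave the evaluable number after loss, so it is the evaluable number divided by (1 − 0.20).

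- 684 / 0.8 = 855
- 686 / 0.8 = 857.5, so 858

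The stated 820 is 35 to 38 patients lower. The requirement exceeds it by 35/820 = 4.3% to 38/820 = 4.6%.

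**3. What 820 delivers if 20% are lost.** 820 × 0.8 = 656, or 328 per arm.

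- Standard error of the difference = 1.4 × √(2/328) = 0.1093.
- 0.3 / 0.1093 − 1.96 = 0.784, which gives power of 78.4% (normal). The t calculation gives 78.2%.
- Smallest difference detectable at 80% power: 2.8016 × 0.1093 = 0.306 (normal), or 0.307 (t).

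**4. Loss that 820 can absorb at 80% power.**

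- 1 − 684/820 = 16.6% (normal)
- 1 − 686/820 = 16.3% (t)

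**5. Ways to arrive at 820.**

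| Route | Total |
|---|---|
| 684 × 1.2 (multiplying by 1 + loss) | 820.8 |
| 686 × 1.2 | 823.2 |
| SD 1.37, which prints as 1.4: 328 per arm (normal), 656 / 0.8 | 820 |
| One-sided 5%: 540 evaluable, / 0.8 or × 1.2 | 675 or 648 |

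If all 820 were evaluable, power would be about 86.6%, so 820 is not the number before the loss allowance. The first and third routes both fit. The article does not allow a choice between them.

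**6. Effect of the planned analysis.** Assume that the analysis of covariance adjusts for baseline HbA1c, that the SD is 1.4 at both times, and that r is the correlation between baseline and 6 months. The residual SD is then 1.4 × √(1 − r²). With 328 per arm, 80% power needs an SD of 1.369 (t), so r = √(1 − (1.369/1.4)²) = 0.21.

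| Assumed r | Residual SD | Power at 328 per arm (normal) |
|---|---|---|
| 0 | 1.400 | 78.4% |
| 0.21 | 1.369 | 80.1% |
| 0.3 | 1.336 | 82.0% |
| 0.5 | 1.212 | 88.7% |

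The article gives no r, so these rows show a range and do not reconstruct the sponsor's calculation.

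**The case against.** The strongest reply is that nothing of substance turns on this. The power gap is 1.6 to 1.8 points. The detectable difference of about 0.307 rounds to the stated 0.3, and the SD that restores 80% rounds to the stated 1.4. That is fair, and it sets the size of the point: a small correction to a stated figure.

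The second reply is that 78% is not the power of the planned analysis. This also stands. The unadjusted figure is the r = 0 case, and a modest correlation takes the planned analysis to 80% or above. It does not reproduce the printed claim, because the paragraph invokes no such gain, but it rules out calling the trial underpowered.

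The third reply is that a condensed article commonly leaves the evaluable number, the inflation formula and the correlation to the full protocol. Agreed: their absence is no fault. What remains is that the printed numbers disagree.

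Two stronger readings are tempting, and the document supports neither.

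- A reader might infer that the loss was certainly applied by multiplying by 1.2. The match to 820.8 is close and the slip is common, but the step is not shown, the t-based number does not match as well, and an unrounded SD near 1.37 with correct division gives 820 exactly.
- A reader might infer that using a baseline SD for a difference in change makes the calculation invalid. With baseline-adjusted analysis of covariance, the treatment effect on change and on the 6-month value is the same quantity. The unadjusted SD is a common simplification and is conservative when the SDs are equal. An unadjusted comparison of change scores is not what the plan specifies.

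**Conclusion.** The stated size, power and loss allowance do not agree on the printed inputs. With a difference of 0.3%, SD 1.4%, a two-sided 5% level and 1:1 allocation, a 20% loss requires 855 to 858 randomised. The stated 820 gives about 78% unadjusted power at that loss, or 80% power at about 16% loss. This rests on taking 1.4 as printed and as the outcome SD, with no gain from covariate adjustment.

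The discrepancy is minor. It does not show that the planned primary analysis has less than 80% power: with baseline HbA1c as covariate and equal SDs, an assumed correlation of about 0.21 or more closes the gap. The abstract's statement that 820 is adequate is therefore not wrong in itself. The origin of the mismatch remains open.

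**What to change.** Keep 820 and restate the sample size sentence in one of two ways.

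- **(a)** On the inputs as printed: 820 randomised, 656 evaluable after 20% loss, about 78% power for a 0.3% difference with SD 1.4%. Equivalently, 80% power with about 16% loss.
- **(b)** On the planned analysis: power of the analysis of covariance for 656 evaluable patients, with residual SD 1.4 × √(1 − r²) and an r that is stated and justified.

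Option (b) is preferable if a credible source for r exists, because the power claim then refers to the analysis that will be run. If the original calculation used a less rounded SD, printing that SD and the evaluable number would also resolve the mismatch.

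The cost is one or two sentences. No extra patients are needed and the design does not change. Under (a) the published figure becomes slightly less favourable.
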